## Abstract

**Introduction::**

Chronic obstructive pulmonary disease (COPD) is a lung disease with the highest incidence and high mortality in the world. Acute exacerbation of chronic obstructive pulmonary disease (AECOPD) can significantly accelerate the progression of the disease. Pulmonary rehabilitation is one of the effective treatment methods in COPD patients, but few studies have focused on the effect of pulmonary rehabilitation in AECOPD patients. Liuzijue can improve the pulmonary function and relieve symptoms of COPD patients. However, due to the influence of disease and non-invasive ventilation (NIV), AECOPD patients have poor compliance with getting out of bed at the early stage. Sitting and lying Liuzijue is more suitable in AECOPD patients with NIV. Therefore, this study will evaluate the effect of sitting and lying Liuzijue for lung function, exercise endurance, and quality of life in AEOPD patients with NIV.

**Methods::**

This study is a clinical randomized controlled trial. Sixty four AECOPD patients with NIV will be randomly divided into the experimental group and the control group. All participants will be treated with routine treatment and nursing according to their specific condition. The experimental group will be combined with sitting and lying Liuzijue on the basis of the control group. The duration of the exercise will be 3 months. The primary outcomes are the pulmonary function test and 6-minute walking test (6MWT). The secondary outcome measures include blood gas parameters, dyspnea index (the Modified Medical Research Council Dyspnea Scale [mMRC]), the body-mass, airflow obstruction, dyspnea and exercise capacity (BODE) index, anxiety, and depression (Hospital Anxiety and Depression Scale [HADS]), and quality of life (St·George Respiratory Questionnaire [SGRQ]). The measurement of outcomes will be evaluated at week 13.

**Discussion::**

It's imperative to focus on pulmonary rehabilitation in AECOPD patients. The purpose of this study is to evaluate the effect of sitting and lying Liuzijue for pulmonary rehabilitation in AECOPD patients with NIV.

**Trial registration::**

ChiCTR2000034530, Registered on July 8th, 2020.

## Introduction

1

Chronic obstructive pulmonary disease (COPD) is a lung disease with the highest incidence in the world.^[1]^ It is estimated that it will be the third leading cause of death, and the economic burden of disease will be the fifth in the world by 2020. The morbidity and mortality of COPD in China are increasing year by year. The results of recent research confirmed for the first time that there are about 100 million COPD patients in China (accounting for about 25% of the total number of COPD patients in the world). The prevalence rate of COPD in people over 40 years old is as high as 13.7%, which is the highest in all countries.^[2]^ In China, the overall disease burden has ranked second. COPD has become the third most common chronic disease after hypertension and diabetes.

Acute exacerbation of chronic obstructive pulmonary disease (AECOPD) is an important course in the clinical process of COPD. It can significantly accelerate the progression of the disease. A study shows that 25% of the decline in lung function of COPD patients can be attributed to AECOPD. The acute exacerbation of COPD could not fully recover their peak pulmonary function flow and health status after 3 months, which seriously affected their work and quality of life.^[3]^

At present, in addition to oxygen therapy and drug therapy, pulmonary rehabilitation is considered to be an effective treatment in COPD patients.^[4]^ For a long time, pulmonary rehabilitation has been used for moderate and severe stable COPD patients. In addition, it is also effective for AECOPD patients after infection controlled and treated with mechanical ventilation.^[5]^ Mohammed et al^[6]^ found moderate and high intensity and continuous aerobic training can not only improve the respiratory function in moderate and severe COPD patient, but also effectively reduce the risk of cardiovascular disease. HE et al^[7]^ selected 66 AECOPD patients to receive pulmonary rehabilitation intervention on the second day of admission until discharge. The intervention group received exercise training (including stretching, endurance strength training) and breathing training (including respiratory control, lip contraction breathing), twice a day, 30 minutes each time. Compared with the baseline, the 6-minute walk test (6MWT) of the intervention group increased by 49 m, and the Brog dyspnea score was significantly improved. Compared with the control group, the Modified Medical Research Council Dyspnea Scale (mMRC) and the body-mass, airflow obstruction, dyspnea and exercise capacity (BODE) index were significantly improved. It is suggested that pulmonary rehabilitation can improve the exercise ability and quality of life of patients. And there are no adverse events in the process of intervention, which confirms the safety of early pulmonary rehabilitation intervention. The 2016 Cochrane evidence-based analysis also shows that pulmonary rehabilitation in AECOPD patients can improve health-related quality of life and exercise endurance.^[8]^

Modern pulmonary rehabilitation program mainly includes: exercise training, breathing training, physical therapy, nutritional support, psychotherapy, health education, and so on. Traditional Chinese medicine (TCM) pulmonary rehabilitation projects mainly include: traditional Chinese medicine, acupuncture, functional exercise, massage, acupoint application, dietotherapy, psychotherapy, and so on. The findings from previous studies suggest that Chinese traditional exercise, including tai chi, liuzijue, wuqinxi, and yijinjing, have positive effect on COPD patients.^[9]^

Liuzijue, a kind of traditional Chinese Qigong, emphasizes the integration of body adjustment, breath adjustment, and heart adjustment in the process of exercise.^[10]^ Liuzijue adopts reverse abdominal breathing, mouth exhale, and nose inhale to match the action. At the same time, emphasizes the role of spirit and ideas. When exhaling, concentrate and think about the viscera corresponding to each word. The 6 sounds of “xu,” “he,” “hu,” “si,” “chui,” and “xi” in Liuzijue correspond to lung, heart, spleen, liver, kidney, and Sanjiao respectively. Respiratory muscles such as intercostal muscle, rectus abdominis muscle, and pectoralis major muscle are mobilized to participate in training so as to deepen respiratory depth and improve pulmonary ventilation.^[11]^ A large number of studies have confirmed that Liuzijue can improve lung function, dyspnea symptoms, exercise endurance, and quality of life in stable COPD patients.^[11–13]^

However, AECOPD patients often have severe dyspnea, respiratory muscle fatigue and respiratory acidosis during hospitalization, so they need to be treated with non-invasive ventilation (NIV).^[14]^ On the other hand, nutrition level and hormone medication will cause patients to feel tired. At the same time, they are also worried that getting out of bed will aggravate their illness.^[15,16]^ Thus AECOPD patients have poor compliance with getting out of bed at the early stage, especially those with NIV. Therefore, it is particularly urgent to explore an effective exercise method suitable for AECOPD patients with NIV. Sitting and lying Liuzijue is a kind of medium and low intensity aerobic exercise which is on the basis of Liuzijue. It is suitable for people who are too old and frail to stand for a long time. Compared with the standing Liuzijue, it is more appropriate for long-term bedridden AECOPD patients with NIV.

Therefore, in this study, sitting and lying Liuzijue will be used to carry out early pulmonary rehabilitation exercise in AECOPD patients with NIV. The purpose of this study is to evaluate the effect of sitting and lying Liuzijue on blood gas index, pulmonary function, dyspnea symptoms, exercise endurance, BODE index, anxiety and depression, and quality of life. Thus, to provide a safe, effective, and good compliance method of TCM pulmonary rehabilitation exercise for AECOPD patients with NIV.

## Methods/design

2

### Design

2.1

This study is a clinical randomized controlled trial. Sixty four AECOPD participants with NIV will be conducted in the Hospital of Chengdu University of TCM (Chengdu, China). Participants will be recruited through a recommendation by the respiratory clinician. The participants will be informed of the benefits and risks of the study in detail. After obtaining written informed consent, eligible participants will be randomly assigned to the experimental group and control group in a ratio of 1:1. To prevent design bias, we will follow the Consolidated Standards of Reporting Trials statement^[17]^ and the Standard Protocol Items: Recommendations for Interventional Trials (SPIRIT) 2013 statement.^[18]^ The study procedure is shown in Fig. 1 and the time points of the study is shown in Fig. 2.

**Figure 1 F1:**
[figure not shown]
Study procedure.

**Figure 2 F2:**
[figure not shown]
Illustration of the design for clinical studies. 6MWT = 6-minute walking test, HADS = Hospital Anxiety and Depression Scale, mMRC = the Modified Medical Research Council Dyspnea Scale, SGRQ = St·George Respiratory Questionnaire.

### Ethics approval

2.2

The study is in compliance with the Declaration of Helsinki (Edinburgh 2000 version). This study was reviewed by the Ethics Committee of the affiliated Hospital of Chengdu University of traditional Chinese Medicine (Ethics No: 2019KL-064), following the principles of voluntariness, impartiality, advantage, and confidentiality. Explain the purpose, scheme, intervention time, benefits, and potential risks of this study to patients before intervention. Strictly abide by the wishes of the patients, agree and sign the informed consent form before entering the research group. In the process of intervention, patients have the right to withdraw from this study according to their own conditions. Strictly implement the termination standard to ensure the safety of patients. Personal information and related records of patients will be kept strictly confidential. We registered the study in the Chinese Clinical Trial Registry (Registration number: ChiCTR2000034530) in 2020. If there is any amendment to the protocol, approval must be again sought from the Ethics Committee.

### Sample size

2.3

The calculation of sample size is based on the main results (6MWT). According to the previous literature,^[19]^ it is estimated that the average score of the control group was 442.5 and the standard deviation was 61.5. After Taiji Qigong exercise, the average of the experimental group was 486.7 and the standard deviation was 67.3. formula for calculating the sample size is as follows: 

At the 5% significance level, a total of 26 patients are needed in each group to achieve 80% power. The estimated dropout rate is 20%, and a total of 32 patients have been included in each group.

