### Statistical analysis

3.6

Two researchers who are not be involved in the recruitment, evaluation, or training of patient will be responsible for entering the data. Statistical analysis will be carried out by using SPSS 24.0 statistical software. If the measurement data accorded with normal distribution, it will be described by mean and standard deviation. If not, it will be described by median and quartile distance. The measurement data will be examined using group *t* tests or non-parametric tests, the count data will be tested using a Chi-square test or Fisher exact probability method, and the grade data will be tested using non-parametric tests. All statistical tests will be bilateral tests and *P* < .05 will be considered to indicate statistical significance.

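### The stated 80% power does not hold: with the protocol's own inputs and its two-sided tests, 26 per group gives about 68% power for the 6-minute walk test

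*Protocol article*

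**What the plan says.** Section 2.3 (Sample size) bases the calculation on the 6-minute walk test. For the control arm, "it is estimated that the average score of the control group was 442.5 and the standard deviation was 61.5"; for the exercise arm, "the average of the experimental group was 486.7 and the standard deviation was 67.3". It concludes: "At the 5% significance level, a total of 26 patients are needed in each group to achieve 80% power". It does not say whether the 5% is one-sided or two-sided, and the formula it announces is not visible in the text at hand. It then allows for losses: "The estimated dropout rate is 20%, and a total of 32 patients have been included in each group".

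Section 3.6 (Statistical analysis) fixes the test. For continuous data, "The measurement data will be examined using group *t* tests or non-parametric tests". On sidedness and level it is explicit: "All statistical tests will be bilateral tests and *P* < .05 will be considered to indicate statistical significance". Section 2.1 gives 1:1 allocation. Section 3.4 lists the walk test as a primary outcome, together with the lung function measures, and places outcome collection at week 13.

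**The concern.** Section 2.3 gives two means, two SDs, a significance level, a power and a number per group. Together with the test and sidedness in section 3.6 and the allocation ratio in section 2.1, these settle the calculation, so the 26 can be checked without outside information. It looked too small for a standardised difference of about 0.69 tested two-sided.

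The walk test is the only outcome used to justify the size of the trial. If the stated power is too high, a non-significant result would be read as coming from an 80%-powered trial and so as fair evidence against a 44 m benefit. The real chance of missing that benefit would be much larger than the protocol implies.

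**Working it through.** **Inputs.** From section 2.3: means 442.5 and 486.7, SDs 61.5 and 67.3, level 5%, power 80%, 26 completers and 32 randomised per group, dropout 20%. From section 3.6: two-sided two-sample t test (or a non-parametric test). From section 2.1: 1:1 allocation. Section 2.3 gives no unit; metres are assumed.

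- Difference: 486.7 − 442.5 = 44.2
- Sum of variances: 61.5² + 67.3² = 3782.25 + 4529.29 = 8311.54
- Pooled SD: √(8311.54 / 2) = 64.47, so d = 44.2 / 64.47 = 0.686

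**Step 1: trying to reproduce 26.** The usual formula is n per group = (z_α + z_β)² × (SD₁² + SD₂²) / difference². The last factor is 8311.54 / 44.2² = 4.254.

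- Two-sided 5%: (1.960 + 0.842)² × 4.254 = 7.849 × 4.254 = 33.4, so 34. The t-based calculation gives 34.4, so 35.
- One-sided 5%: (1.645 + 0.842)² × 4.254 = 6.183 × 4.254 = 26.3. The t-based calculation gives 27.0.

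Other SD choices do not bring the two-sided number down to 26: the control SD alone gives 31, the average SD 34, and the experimental SD alone 37. The one-sided result is the closest match, but it reaches 26 only if 26.3 is rounded down.

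**Step 2: power under the planned test.** In the normal approximation, power = Φ(44.2 / √(8311.54 / n) − 1.960). At n = 26 the standard error is √(8311.54 / 26) = 17.88, the ratio is 44.2 / 17.88 = 2.472, and Φ(0.512) = 0.696. The t-based column uses the noncentral t distribution.

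| Evaluable per group | Two-sided power, t test | Two-sided power, normal |
|---|---|---|
| 25 | 66.1% | 67.9% |
| 25.6 (32 × 0.8) | 67.2% | 68.9% |
| 26 | 67.9% | 69.6% |
| 32 (no dropout) | 77.0% | 78.3% |
| 34 | 79.6% | 80.7% |
| 35 | 80.7% | 81.8% |

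**Step 3: detectable difference.** At 26 per group, the difference detectable with 80% two-sided power is about 51 m by the t test. By the normal formula it is 2.802 × 17.88 = 50.1 m. Both exceed the 44.2 m on which the trial was sized.

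**Step 4: dropout.** 32 × 0.8 = 25.6, slightly below 26. In power this is 67.2% against 67.9% (t test).

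**Step 5: what a baseline-adjusted analysis would need.** Adjustment multiplies the residual variance by (1 − ρ²), where ρ is the correlation between baseline and week 13. To detect 44.2 m with 80% power where the unadjusted t test detects 51.1 m (26 per group), 1 − ρ² = (44.2 / 51.1)² ≈ 0.75, so ρ ≈ 0.50. At 25 per group the unadjusted figure is 52.1 m and ρ ≈ 0.53. The article gives no value for ρ.

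**The case against.** A reader might infer that the sponsor used a one-sided calculation, or that one-sided testing is the only reading that yields 26. The document does not establish either. Section 2.3 is silent on sidedness and its formula cannot be seen. A one-sided calculation gives 26.3, normally rounded up to 27, and one-sided t-test power at 26 is 78.6%. This limits what can be said about the cause. It leaves the mismatch untouched: whatever formula was used, 26 per group does not give 80% power under the test in section 3.6.

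A reader might also count the dropout step as a second defect, since 26 / 0.8 = 32.5 rounds up to 33 while the article has 32 (26 × 1.2 = 31.2 rounded up would give it). The gap before rounding is half a patient per group and costs less than one percentage point of power. It is a minor note. Re-inflating 26 to 33 would also start from a number that is itself not the one needed for 80% power.

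Two further points are fair. The shortfall depends partly on the assumed 20% dropout occurring: with complete follow-up, power is 77-78%, close to nominal though still below it. And low power neither biases the estimate nor raises the type I error. Both points bear on how serious the problem is, but neither makes the stated 80% correct.

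**Conclusion.** The point holds as a mismatch between a stated power and a stated test. On the article's own inputs, 26 per group gives 67.9% (t test) to 69.6% (normal approximation) two-sided power, so the type II error is about 30-32% instead of 20%. Reaching 80% takes 34 to 35 completers per group, which is 8 to 9 more than stated. After the assumed dropout, power is about 67-69%.

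This rests on an unadjusted comparison of week-13 values with the SDs in section 2.3. Section 3.6 describes no adjustment that would restore the power. The mismatch is certain from the arithmetic; a one-sided origin for the 26 is only the likeliest explanation. A reader should not conclude that the trial is invalid or its estimate biased. What is wrong is the power claim, and with it the weight that a null walk-test result could carry.

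**What to change.** Keep 32 randomised per group and restate section 2.3:

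- The test is two-sided at 5%.
- With 20% dropout, about 25 to 26 per group are evaluable.
- Power is then about 67-69% for 44.2 m, or 80% for about 51 m.
- If nobody drops out, power for 44.2 m is 77-78%.

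Do not change the dropout step to 33. This costs a rewording of one section and a less favourable power statement; no further patients are needed.

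Optionally, change section 3.6 so that the walk test is analysed by ANCOVA with the baseline value as covariate. Section 2.3 should then say that 80% power at 25 to 26 per group requires a baseline to week-13 correlation of about 0.5 (0.50 to 0.53), and label this an assumption, since the article gives no support for a value. This costs a change to the analysis section as well, which under section 2.2 needs renewed ethics approval as a protocol amendment.

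For comparison, keeping 80% with the unadjusted two-sided test would take 34 / 0.8 = 42.5 to 35 / 0.8 = 43.75, that is 43 to 44 randomised per group, or 86 to 88 in total against the 64 planned.

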### Participants

2.4

#### Diagnostic criteria

2.4.1

1.The diagnostic criteria of COPD are as follows: Refer to the guidelines for the diagnosis and treatment of chronic obstructive Pulmonary Disease (revised in 2013) and the global initiative for chronic obstructive pulmonary disease (GOLD) in 2019.2.The diagnostic criteria of AECOPD are as follows: Patients with acute exacerbation of respiratory symptoms (typically characterized by increased dyspnea, increased cough, increased sputum and/or purulent sputum), beyond daily variation, and led to the need to change the drug treatment regimen.3.The standards of NIV are as follows: Respiratory acidosis (arterial blood pH ≤7.35 and/or PaCO_2_ >45 mmHg). Severe dyspnea combined with clinical symptoms. Increased respiratory function, such as the application of auxiliary respiratory muscle breathing, chest-abdominal contradictory exercise, or costal space muscle contraction.

#### Inclusion criteria

2.4.2

1.Patients with COPD diagnosed according to GOLD.2.AECOPD patients with NIV.3.Age range 40 to 80 years.4.Clear consciousness for communicating normally and completing the self-rating scale.5.Agree to sign the informed consent and voluntary participation.

Only those who conform to all of the above criteria will be included.

#### Exclusion criteria

2.4.3

1.Patients with chronic cough and asthma caused by lung cancer, pulmonary interstitial disease, bronchiectasis, bronchial asthma, and other non-chronic obstructive pulmonary diseases.2.Intolerant to exercise (complicated with severe diseases of cardio-cerebrovascular, liver, kidney, lung and hematopoietic system).3.Patients with functional impairment of low back and limbs or after operation.4.Patients with mental illness or speech disorder to communicate difficultly.5.Patients who are currently participating in other clinical studies or doing other functional exercises.

Those who conform to any of the above criteria will be excluded.

#### The termination and withdrawal criteria

2.4.4

1.Voluntary withdrawal from the trial or loss of follow-up.2.Poor compliance.3.Emergency attack of serious illness during the study and need other treatment.

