### The experimental group

3.2

On the basis of the control group, participants in the experimental group will practice sitting and lying Liuzijue once every morning and evening, 30 minutes each time, for a total of 3 months. Before the official start of the experiment, 2 members of the research group need to be trained in skills and methods. After successfully passing the examination, they would conduct action guidance and training to the participants. The teaching time of patients should be controlled within 5 days, and they should be assessed on the last day. After the patients have correctly mastered the steps, essentials and matters needing attention of sitting and lying Liuzijue, they will formally enter the experiment.

Sitting and lying Liuzijue exercise begin immediately after the appearance of the lung infection control window. Exercise once every morning and evening, each time for 30 minutes, for a total of 3 months. In the process of exercise, the participants need to take off the NIV mask and use nasal catheters to inhale oxygen. The pulse oxygen saturation meter will be used to closely monitor the changes of heart rate and fingertip oxygen saturation. Take continuous exercise and intermittent exercise according to the tolerance of participants. The next day, ask the participants about their physical recovery and observe their breathing and heart rate during the entire exercise to confirm whether the current exercise intensity is appropriate.

All participants use reverse abdominal breathing, exhale first and then inhale. Read when they exhale, lift the anus and contract the kidney at the same time (abdomen and buttocks, urethral orifice, and anal micro-lift). When inhaling, the lips are gently closed, the tongue is against the upper jaw, the whole body is relaxed, the lower abdomen is naturally raised, and the air is naturally inhaled. After reading each word 6 times, using natural breathing, tongue against the palate (cis-abdominal breathing can also be used). The function is to adjust breathing, restore nature, and take a short rest. The detailed steps are shown in Fig. 3.

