### Compliance

3.3

Keep communication effectively with participants and establish a good relationship. Inform participants the importance of practicing sitting and lying Liuzijue for disease recovery. During hospitalization, members of the research group will guide and supervise participants every day. When the participants are discharged from hospital, distribute “intervention diary” and conduct guidance and supervision through telephone and WeChat groups. If the participants are not motivated enough during the trial, they would be encouraged and the frequency of supervision would be increased. In the process of intervention, participants can share and communicate with each other through WeChat groups for promoting compliance.

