### Outcome measures

3.4

The primary outcomes are the pulmonary function test (FEV_1_%, FEV_1_/FVC, and FVC) and 6-minute walking test (6MWT). The secondary outcome measures include blood gas parameters (PH, PaCO2, PaO2), the mMRC, Hospital Anxiety and Depression Scale (HADS), and St·George Respiratory Questionnaire (SGRQ). Baseline data will be collected before intervention. Outcome indicators will be collected at the 13th week.

The measurement of pulmonary function will be carried out by the same pulmonary function technician in the respiratory department. Before the test, the participants need to take a rest quietly for 10 minutes, then inhaled the bronchodilator salbutamol 200 μg. The arterial blood will be collected by the nurses in the department for blood gas analysis. 6MWT will be carried out by trained team members. Before the test, the participants need to take a rest for 10 minutes, and their blood pressure, pulse, and blood oxygen saturation will be measured. Carry a portable pedometer and walk as fast as possible. At the end of time, blood pressure, pulse, and blood oxygen saturation will be measured again, and the walking distance will be recorded. All the scales involved in this study will be completed by 3 specialized researchers who had received professional training and passed the examination.

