However, it can not be ignored that this study also has some limitations. First of all, the study is a kind of sports intervention. It is difficult to achieve the blind method of implementers and participants, so there may be a placebo effect leading to deviation. Secondly, sitting and lying Liuzijue is a kind of traditional Chinese exercise, so the cognition of it will be limited by geography, which may hinder its application and promotion. Finally, the participants in the study will be all from the same hospital in Sichuan, China. It's not clear whether the relative effects of the sport in other ethnic groups are similar. However, despite the limitations, we believe that this study is expected to confirm that sitting and lying Liuzijue can improve lung function, exercise endurance, quality of life, and create better social benefits in AECOPD patients with NIV.

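### Poor compliance and emergency illness end trial participation rather than only the exercise, which is liable to bias the week-13 6MWT comparison

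*Protocol article*

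**What the plan says.** Section 2.4.4 (The termination and withdrawal criteria) is one list: "1.Voluntary withdrawal from the trial or loss of follow-up.2.Poor compliance.3.Emergency attack of serious illness during the study and need other treatment". It does not distinguish stopping the exercise from leaving the trial. Section 2.2 (Ethics approval) adds: "Strictly implement the termination standard to ensure the safety of patients".

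Section 3.3 (Compliance) deals with the study exercise. It begins with rapport and with this instruction: "Inform participants the importance of practicing sitting and lying Liuzijue for disease recovery". Daily supervision in hospital, then a diary, telephone contact and WeChat groups after discharge, follow from that. Only one arm has this exercise to do. Section 3.2 gives the schedule, in which the closing figure counts months: "participants in the experimental group will practice sitting and lying Liuzijue once every morning and evening, 30 minutes each time, for a total of 3".

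On timing, section 3.4 (Outcome measures) says: "Outcome indicators will be collected at the 13th week". Apart from baseline, no other assessment is described. Section 3.6 compares the groups by a two-sample t test or a non-parametric test. Section 2.3 (Sample size) asks for 26 per group and enrols 32, because "The estimated dropout rate is 20" per cent. The Discussion concedes on blinding: "It is difficult to achieve the blind method of implementers and participants".

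**The concern.** Randomisation protects the comparison only if the patients measured at week 13 are the patients randomised, or differ from them in the same way in both arms. Section 2.4.4, followed as written, ends participation before the only post-baseline measurement for two reasons that may break this condition.

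- **Poor compliance** is plausibly tied to arm. The monitoring in section 3.3 is monitoring of Liuzijue, and staff know who is assigned to it. It is also plausibly tied to outcome: the Introduction links reluctance to leave bed in these patients to illness and tiredness, which would also shorten a walk.
- **Emergency illness** is plausibly tied to outcome in patients recovering from an exacerbation that needed NIV.

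At stake is whether a difference at week 13 reflects the exercise or the selection of those who kept it up. The same rule bears on the other primary outcome, pulmonary function, but the article gives no figures from which to illustrate that.

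**Working it through.** **Inputs from the article (section 2.3).** 6MWT mean 442.5, SD 61.5 (control); mean 486.7, SD 67.3 (experimental). The design difference is 486.7 − 442.5 = 44.2 m. The common SD is √((61.5² + 67.3²)/2) = 64.47 m. There are 32 per arm, and 20% dropout is expected.

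**The plan's own figure.** n per group = 2 × [SD × (z for alpha + z for power) / difference]². At 5% one-sided and 80% power this gives 26.3, so the stated 26 is reproduced to within rounding. At 5% two-sided it gives 33.4, rounded up to 34. For dropout, 26 × 1.2 = 31.2, rounded up to 32. The sidedness question is a separate matter and does not affect this point. The 20% is an overall dropout figure that does not separate causes or arms.

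**Assumptions not in the documents.** There is no true effect. A fraction p of the experimental arm, the least compliant, goes unmeasured, and no controls do. Compliance and week-13 6MWT have correlation r. The values r = 0.3 to 0.5 and p = 10% or 20% are chosen for illustration.

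**Shift in the experimental mean** = r × SD × φ(z_p)/(1 − p), where φ is the standard normal density and z_p its p-quantile.

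- p = 0.20: φ/(1 − p) = 0.2800/0.8 = 0.350, and 0.350 × 64.47 = 22.6 m. Times 0.3 this is 6.8 m; times 0.5 it is 11.3 m.
- p = 0.10: 0.1755/0.9 = 0.195, and 0.195 × 64.47 = 12.6 m. Times 0.3 this is 3.8 m; times 0.5 it is 6.3 m.

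Against 44.2 m, the 20% case amounts to 15 to 26% of the design difference (6.8/44.2 and 11.3/44.2). The 10% case amounts to 9 to 14%.

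**Two-sided type I error at p = 0.20.** 32 × 0.8 = 25.6 experimental patients remain against 32 controls. SE = 64.47 × √(1/25.6 + 1/32) = 17.1 m. The shift divided by the SE is 0.40 (r = 0.3) or 0.66 (r = 0.5). The probability of exceeding ±1.96 is then 6.8% or 10.1%.

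**Check by simulation** (8,000 trials per scenario, 6 of 32 removed per affected arm, t test):

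| Scenario | r | Mean bias (m) | Rejection rate |
|---|---|---|---|
| Experimental arm only | 0 | −0.2 | 5.0% |
| Experimental arm only | 0.3 | 6.4 | 6.6% |
| Experimental arm only | 0.5 | 10.6 | 10.0% |
| Both arms equally | 0.3 | −0.1 | 5.4% |
| Both arms equally | 0.5 | 0.2 | 6.0% |

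The simulation agrees with the formula. It also shows that the bias in the mean needs both ingredients: removal related to outcome, and removal that differs between arms.

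**The case against.** The strongest objection is that the article never says withdrawn patients go unmeasured or are left out of the test, and that an unseen SAP may define an analysis of all randomised patients. The absence of an analysis set from a journal article is indeed no fault. But the withdrawal rule is stated, not omitted, and an analysis set cannot supply a week-13 walk that was not done because participation had ended.

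Several stronger readings are tempting, and the documents do not support them.

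- *The sample size plans to analyse only 26 per group.* It does not. Raising 26 to 32 is ordinary inflation for dropout.
- *Only the experimental arm can lose patients for poor compliance.* Section 3.3 promotes compliance rather than defining it, and controls also have breathing exercises (section 3.1). Removal mainly from the experimental arm is likely, not certain. Section 3.3 also answers low motivation with encouragement and closer supervision, which should reduce removals.
- *Illness removal adds to a bias in favour of Liuzijue.* The rule covers both arms. If the exercise prevented relapse, more controls with poor outcomes would be removed, and the bias would run against Liuzijue.
- *Relapses are hidden.* Section 3.5 requires adverse events to be recorded in detail, and nothing exempts an illness that leads to withdrawal.

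The correlation and the one-arm removal are also assumed, so the metres above are conditional.

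**Conclusion.** The point holds as a risk built into a stated conduct rule. Section 2.4.4 makes poor compliance and emergency illness grounds for leaving the trial, and nothing in the article brings such patients back at week 13. The compliance ground is liable to bias the 6MWT comparison, most plausibly towards Liuzijue; that direction rests on poor compliers being mainly in the experimental arm and walking less far. The illness ground selects on outcome, with unknown net direction.

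Neither the size nor the direction can be derived from the documents. Under the stated assumptions the bias is a modest part of the design difference, and it can be about zero. The reason to act is that measurements not taken under this rule cannot be recovered at the analysis stage.

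**What to change.** Reword section 2.4.4 so that poor compliance and intercurrent serious illness may end the exercise but not trial follow-up. Only withdrawal of consent or true loss should end follow-up. Assess all other randomised patients at week 13 where possible. Make the primary analysis all randomised patients as allocated, with any analysis of compliers secondary. Report deaths and serious illness by arm. This leaves the decision on when to stop the exercise where it is; it changes only whether the patient is still measured and counted.

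The cost is a protocol amendment with ethics approval, which section 2.2 requires for any change, and a few more week-13 visits. The estimated effect may be smaller because non-compliers stay in. If the full protocol already keeps these patients in follow-up, one clarifying sentence in section 2.4.4 is enough on that part.
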